## Abstract

**Background:**

Research has shown that obese individuals have cognitive deficiencies in executive function, leading to poor planning and impulse control, and decision-making difficulties. An intervention that could help reduce these deficits and in turn help weight loss maintenance is Cognitive Remediation Therapy for Obesity (CRT-O). We aim to examine the efficacy of manualised CRT-O, which is intended to improve executive function, enhance reflective practice and help weight loss maintenance.

**Methods/Design:**

A randomised controlled trial (registered with the Australian New Zealand Clinical Trials Registry) will be conducted. First, 90 obese adults (body mass index >30 kg/m^2^) in the community will receive three weekly sessions of a group Behaviour Weight Loss Treatment (BWLT), and then will be randomised either to receive CRT-O or to enter a no-treatment control group. CRT-O training will comprise twice-weekly sessions of 45 minutes over a 4 to 6 week period, for a total of eight sessions. Measurement points will be at baseline, post CRT-O (or 4 to 6 weeks after BWLT for the no-treatment control), 3 months post treatment and 1 year post treatment. The primary outcome will be executive function and secondary outcome measures will include participants’ body mass index, hip to waist ratio, eating behaviours and quality of life.

**Discussion:**

This is the first study of its kind to examine the efficacy of Cognitive Remediation Therapy for obese adults through a randomised controlled trial.

**Trial Registration:**

Australian New Zealand Clinical Trials Registry number: 12613000537752. Date of registration: 14 May 2013.

## Background

Approximately 1 billion adults are currently overweight (body mass index (BMI) 25 to 29.9 kg/m^**2**^) and a further 475 million are obese (BMI >30 kg/m^2^) [1]. Ranking second only to smoking as a preventable cause of death, obesity contributes to over 300,000 deaths per year [2]. Obesity is also associated with a wide range of medical and psychological sequelae, eating disorder behaviours such as binge eating and subsequent impaired health-related quality of life (HRQoL) [3–5]. Although 5% to 10% weight loss is associated with clear health benefits, the prevention of weight regain has remained a challenge. Even with the help of professionals and extended behavioural treatments, weight regain typically occurs when professional contact ends [6]. By 3 to 5 years post-treatment, about 85% of patients have regained weight or even exceeded their pre-treatment weight [7].

Empirical research has found obesity to be associated with cognitive impairment, especially in executive function, irrespective of the presence of binge eating [8] and independent of co-morbid medical conditions such as diabetes, hypertension and cancer, which are themselves associated with adverse cognitive effects [9, 10]. Executive function encompasses a range of cognitive processes facilitating initiation, planning, regulation, inhibition, sequencing and achievement of complex goal-oriented behaviour [11]. The association of obesity and executive deficits is found across the age span, in children, adolescents, older adults, middle-aged adults and young adults [12–14]. A review [15] found that the evidence is highly consistent, with 22 out of 24 studies showing a negative association between obesity and cognition, especially in executive function. For example, inhibitory control, an aspect of executive function, involves the suppression of actions that are contextually inappropriate and interfere with behavioural goals. Studies of obese adults in the community have found executive deficits to be positively associated with disinhibited eating and greater food cravings [16]. Furthermore, obese individuals have been found to demonstrate cognitive impulsivity, an autonomic readiness to make quick decisions, which prevents successful inhibition of a prepotent behavioural response. It has been shown that impulsive subjects have marked limitations for learning suitable associations between reward and punishment [17, 18] and as a result they are more influenced by immediate rewards than by future consequence [18]. Hence, executive deficits have been shown to impair the capacity for impulse regulation, including control over the impulse to eat excessively [19]. Furthermore, evidence indicates a positive association between a higher BMI and decision-making impairments [20]. Findings from a study on the decision-making profiles of obese adult females using the Iowa Gambling Task showed a preference for high immediate reward, despite higher future losses in terms of both physical and psychological outcomes [18]. Studies have also shown that obese individuals perform similarly on the Iowa Gambling Task as those with anorexia nervosa, for example, see [21], and as patients with orbitofrontal dysfunction [22], and worse than those who are substance dependent [23]. While executive function deficits have been shown to be similar in anorexia nervosa and obesity, obese individuals show worse performance in the inhibition response measured by the Stroop test compared to individuals with anorexia nervosa or healthy controls [24].

The mechanism by which obesity is associated with cognitive function is, however, unclear at present [8]. Smith and colleagues [15] suggested a bidirectional relationship between obesity and executive function, where obesity impairs executive function via biological mechanisms, such as inflammatory markers or glucose abnormalities, and impaired executive function impacts on obesity by causing an inability to regulate food intake, plan ahead, inhibit responses or act impulsively. There is some evidence for this bidirectional association. One longitudinal study showed that poor executive function at age four predicted a high BMI at age six [14]. It is possible, based on the evidence presented above, that cognitive deficiencies may contribute to increased adiposity by exacerbating weight gain or regain after weight loss, and targeting these deficits in the obese has the potential to improve participants’ response to therapy. This led to the development of a novel treatment for weight disorders, namely Cognitive Remediation Therapy for Obesity (CRT-O) [15, 25].

CRT-O is a manualised treatment derived from Cognitive Remediation Therapy (CRT), which is used to treat people with addiction, feeding or eating disorders. In trials of people with a substance-use disorder, computer-assisted CRT has been shown to reduce individuals’ need for immediate reward and improve their decision-making [26]. Experimental studies have shown that practicing inhibitory control, an aspect of executive function, reduces the consumption of high-calorie foods [12, 27, 28]. Specifically, studies have shown that improving inhibition of behaviour towards high-calorie items, via a computerised go/no-go task, reduced the consumption of palatable foods across a 1-day period [12, 28]. Similarly, manualised Cognitive Remediation Therapy for Anorexia Nervosa (CRT-AN) has been shown to be associated with cognitive improvements in addition to improvements in eating-disorder-related quality of life at the end of treatment and eating-disorder psychopathology at a 6-month follow-up [29]. Furthermore, there were low dropout rates and high levels of acceptability among both patients and therapists [30].

Like CRT-AN, CRT-O is designed to provide individuals with the tools to think differently about their cognitive style and how they address food. However, in CRT-O the intent is to help maintain weight loss and prevent further weight gain by linking the thinking style to food intake and exercise behaviours. CRT-O is a brief eight-session individual therapy where simple cognitive tasks and exercises that encourage reflective learning and insight into a participant’s own thinking process are administered together with intra-session experimentation. The rationale being that this will improve various aspects of executive function, including cognitive flexibility, central coherence (attention to detail) and problem-solving and will in turn improve participants’ ability to follow the guidelines of a behavioural weight-loss programme. Supporting this are promising results from a small trial (*n* =44) by Verbeken *et al*. [12], testing executive function training with games in children. In this study, moderate to large effect sizes (standardised mean differences between 0.5 and 0.6) were found in executive function outcomes, such as improvements in a behaviour rating inventory of executive function and in a working memory task that favoured training. However, there were smaller effects for a task assessing response inhibition. To our knowledge the efficacy of this approach has not yet been investigated in adults.

We have designed the present randomised controlled trial (RCT) to test the efficacy of manualised individual face-to-face CRT-O as developed by Smith and colleagues [25]. The primary outcome in this superiority trial is improvement in executive function demonstrated at end of treatment and at 3 months, and maintained at the 1-year follow-up. Secondary outcomes are participants’ BMI, hip to waist ratio, eating behaviours and quality of life. Since studies on anorexia nervosa have found an improvement in quality of life, we wish to examine whether quality of life improves after CRT-O. In this RCT, all participants receive standard care for weight loss, namely group-based Behaviour Weight Loss Treatment (BWLT), and are then randomised to a CRT-O group or a no-treatment control group. CRT-O targets executive function deficits and changes in thinking style, whereas BWLT targets health literacy and weight-loss strategies including psycho-education, weight monitoring, dietary advice and exercise planning. Perceived barriers to weight management are discussed and challenged.

The primary hypothesis is that, compared to those who receive BWLT only, participants who receive BWLT plus CRT-O will demonstrate improved executive function post treatment, which is maintained at the 3-month and 1-year follow-ups. The secondary hypotheses are that that executive function changes will predict changes in weight, and compared to those who receive BWLT only, participants who receive BWLT plus CRT-O will have improved (i) weight loss (assessed by BMI and hip to waist ratio), (ii) HRQoL and (iii) dietary habits (including reduced binge eating) at post treatment and maintained at the 3-month and 1-year follow-ups.

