#### Neuropsychological assessment

The six neuropsychological tests employed are selected because they cover different aspects of executive functioning and are commonly used in clinical and research settings. The tests are administered individually to all subjects by a trained clinical psychologist or neuropsychologist.The Wisconsin Card Sorting Test (WCST) 64: The computerised version of WCST [32–34] will be used. In this test, subjects are instructed to categorise a series of cards according to one of three stimulus features (colour, shape or number of illustrations on them), without this principle being revealed to the subject. After each association, the only feedback given is whether a match is correct or incorrect, the idea being that subjects should infer how to categorise based on the feedback they receive. This test measures categorisation, inference, testing of hypotheses, cognitive flexibility, cognitive inhibition and response to feedback [16]. The number of total errors and perseverative errors and failure to maintain a set are the dependent measures. WCST is considered to be a valid measure of abstract reasoning ability to maintain an appropriate planning and problem-solving strategy across changing stimulus conditions to achieve a future goal, and it is the most widely used test of executive function [35].Digit Span, a subtest of the Wechsler Adult Intelligence Test III [36]: In this test, the subject is presented with a series of digits to be repeated in the same order (Digit Span Forward) followed by another series to be repeated backwards (Digit Span Backward). Digit Span Forward assesses the phonological loop and Digit Span Backward assesses central executive aspects of the verbal working memory [37]. The score is calculated based on the number of correct responses that could be immediately retained.Trail Making Test (TMT) [38]: This will be used to assess psychomotor speed, visual integration, cognitive flexibility and inhibitory control. This test measures the subject's ability to connect written numbers in an ascending order (Trail A), and, afterwards, to connect numbers and letters, alternating numbers in ascending order and letters in alphabetical order (Trail B), for example, 1-A-2-B. The score is the response time taken to complete the respective trails [35].Computerised Reward–Loss Task [39]: This is a probabilistic classification task that assesses decision-making. In each trial, participants view one of four images and are asked to guess whether it belongs to category A or B. In the reward-learning task, if the participant correctly guesses the category membership for a trial, a reward of +25 points is received. If the participant guesses incorrectly, no feedback is given. In the punishment-learning task, if the participant guesses incorrectly for a trial, a punishment of -25 points is received, and correct guesses receive no feedback. The reward and punishment trials are intermixed so that no-feedback trials are ambiguous. The ±25 points symbolise quarter dollars that are won or lost, but no real payments are used in this study. The dependent variables are the number of errors made and completion time.Behaviour Rating Inventory of Executive Function, Adult Version (BRIEF-A) [40]: This is a widely used, standardised measure based on a multidimensional model of executive function and the only available self-report measure of executive function at present. The BRIEF-A captures information on an adult’s executive functions or self-regulation in his or her everyday environment.Rey–Osterrieth Complex Figure Test [41, 42]: This test (both copy and a 3-minute recall) will be used to measure attention to detail (central coherence), perceptual and organisational skills, and nonverbal memory. Scores will be calculated for the copy and 3-minute delay portions of the test using the scoring manual.

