### Data collection, management and analysis

Data is collected at baseline, end-of-treatment and the 3-month follow-up by the trial therapist. An independent assessment, blind to intervention group, will be made at the 1-year follow-up. Data is entered, cleaned and coded by a research assistant, blind to group allocation, and stored at a secure university facility according to university protocols. An independent statistician will conduct all preliminary analyses. The Statistical Package for Social Sciences (SPSS) statistics will be used.

Neuropsychological measures will first be examined independently and will then be integrated in an executive function composite following the procedure recommended by Rosnow and Rosenthal [79, 80] and applied by Clark *et al*. [81]. The composite score will be generated by converting each executive function scale across all assessment points to *z*- scores, and then averaging across the measures.

Descriptive statistics will be used to present demographic and clinical data including eating disorder features. Baseline univariate between-group tests will be used to compare outcome variables and clinical and demographic data for the groups. Data will be analysed following the intention-to-treat principle. Linear mixed effects modelling [82] will be used to test for between-group differences in the continuous outcome measures, namely the composite scores of cognitive function, waist circumference and BMI, and potential confounds (e.g., levels of depression, anxiety, stress and emotion dysregulation). Generalised estimating equations [83] with a logit response function, or logistic regression, will be used for dichotomous outcomes, such as achieving a 5% reduction in body weight. Effect sizes between and within the two groups will be calculated with Cohen’s *d* computed with the pooled standard deviation, and the odds ratio will be presented where appropriate.

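### No deciding measure, visit or contrast is fixed for executive function, so the 5% error rate is not guaranteed and the 0.80 power was not computed for the three-visit claim

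*Protocol article*

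**What the plan says.** All references are to the protocol article.

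- **Abstract, Methods/Design:** "The primary outcome will be executive function". This is a construct, not a variable.
- **Background:** "The primary outcome in this superiority trial is improvement in executive function demonstrated at end of treatment and at 3 months", with maintenance at 1 year added in the same sentence. The primary hypothesis is that participants given the added therapy "will demonstrate improved executive function post treatment, which is maintained at the 3-month and 1-year follow-ups".
- **Neuropsychological assessment:** "The six neuropsychological tests employed are selected because they cover different aspects of executive functioning". Several tests give more than one score. For card sorting, "The number of total errors and perseverative errors and failure to maintain a set are the dependent measures".
- **Data collection, management and analysis:** "Neuropsychological measures will first be examined independently and will then be integrated in an executive function composite". The linear mixed model is then assigned to the continuous outcomes, "namely the composite scores of cognitive function, waist circumference and BMI". The composite is the only executive function outcome listed there, but it stands beside two anthropometric measures and is not called primary.
- **Participants:** 45 per group, from an effect size of 0.6, power 0.8, a one-tailed test at 0.05 and 20% attrition. No measure or visit is attached to the effect size.

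**The concern.** A 5% error rate and an 80% power belong to a defined decision rule. Here the ingredients (six tests, a composite, three post-randomisation visits) are listed, but the rule that turns them into success or failure is not.

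Two different problems follow, depending on how the gap is filled. If one significant visit or one significant test is enough, the chance of a false positive conclusion exceeds 5%. If all three visits must be significant, as the hypothesis is most literally worded, the trial could miss its primary hypothesis even when the assumed effect is present throughout, because the sample size was set for one comparison.

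Mixed results are foreseeable. The Background reports that the small trial in children behind the effect size found 0.5 to 0.6 on some executive measures and smaller effects on response inhibition. The plan does not say how such a pattern would be read.

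**Working it through.** **Inputs from the document:** d = 0.6, power 0.80, one-tailed 0.05 and 20% attrition (Participants); six tests (Neuropsychological assessment); three post-randomisation visits (Background, Assessment). **Assumed, because the document gives no correlations:** 0.2 to 0.5 between tests and 0.6 to 0.7 between visits for the error rates; 0.4 to 0.8 between visits for power.

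**1. Reproducing the stated sample size.** For one one-tailed two-group comparison, n = 2(1.645 + 0.842)² / 0.6² = 34.3, so 35 per arm. The t-test version gives 35.04, so 36. Then 36 / (1 − 0.20) = 45 per group, as stated. The two-sided versions give 55 (normal) or 57 (t) and do not match. The arithmetic is right, for one test.

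**2. Power of that one test.** With 36 evaluable per arm the noncentrality is 0.6 × √(36/2) = 2.546, and the power is Φ(2.546 − 1.645) = 0.82 (0.81 by the t-test).

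**3. Error rate if any win counts.** Correlated normal test statistics were simulated under no effect (400,000 draws), each compared with 1.645. The composite is the standardised mean of the six.

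| Rule | Error rate |
|---|---|
| Composite at one named visit | 0.05 |
| Composite at any of 3 visits | 0.10 to 0.11 |
| Any of 6 tests at any of 3 visits | 0.33 to 0.45 |

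The upper end of the last row is at correlations 0.2 between tests and 0.6 between visits; the lower end is at 0.5 and 0.7.

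**4. Error rate if all three visits must be significant.** This cannot exceed 5%, because each visit must pass its own 5% test. With no effect at any visit it is 0.3% to 1.7% for between-visit correlations of 0.4 to 0.8.

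**5. Power if all three visits must be significant.** True d = 0.6 at every visit, 36 per arm, one-tailed 0.05.

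- *Unadjusted comparisons.* Each visit has noncentrality 2.546. Joint power is 0.62 at correlation 0.4, 0.64 at 0.5, 0.68 at 0.7 and 0.71 at 0.8. To reach 0.80, 50 evaluable per arm (63 per group after attrition) would be needed at correlation 0.5, or 45 (57 per group) at 0.8.
- *Baseline-adjusted comparisons.* Suppose baseline correlates with each later visit as the later visits do with each other (r). The noncentrality becomes 2.546 / √(1 − r²) and the correlation between visits becomes r / (1 + r). At r = 0.6 these are 2.546 / 0.8 = 3.18 and 0.375. Joint power is 0.70, 0.77, 0.85 and 0.93 at r = 0.4, 0.5, 0.6 and 0.7. It therefore crosses 0.80 between r = 0.5 and r = 0.6.

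**The case against.** Four points can be made for the plan.

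- **The composite is probably meant to decide.** It is the only executive function outcome named for the mixed model, and averaging tests into one score is a standard way to avoid multiplicity. A reader might infer that every test is a formal success criterion, but examining measures independently does not say that. This stands, so the 0.33 to 0.45 range describes a reading left open, not a stated rule. Even so, the composite is never called primary, and naming it would still leave the visit open.
- **The wording is a conjunction over visits.** A reader might infer that the error rate and the power both fail for the stated claim. The document does not support that: the inflated error belongs to any-win readings and the lost power to the all-visits reading. Under the conjunction the 5% holds.
- **The power loss depends on the analysis.** Baseline is measured and a mixed model is planned, so baseline adjustment could restore 0.80. Later dropout also helps: with 45, 40 and 36 per arm at the three visits, unadjusted joint power is 0.67 to 0.75. Maintenance could also mean description after one post-treatment test, in which case the 0.82 applies. So it is not established that the trial is underpowered. What stands is that the stated power was not computed for the three-visit claim and that the intended reading is not given.
- **A separate analysis plan may settle multiplicity.** Contrasts and adjustments can be left to it. But the primary outcome, the primary hypothesis and the sample size are all stated here, and they do not describe the same test.

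**Conclusion.** The point holds in a limited form. The article defines the primary outcome as a construct over three visits, plans both individual and composite looks at it, and sizes the trial for one comparison tied to neither a measure nor a visit. The 5% error rate is therefore not guaranteed: it is about 0.10 to 0.11 if any visit on the composite may count, and about 0.33 to 0.45 if any test at any visit may count. If all three visits are required, error is controlled, but the 0.80 does not describe that claim: power is about 0.62 to 0.71 unadjusted and about 0.70 to 0.93 with baseline adjustment at correlations of 0.4 to 0.7. All these ranges rest on assumed correlations, and the power figures also on d = 0.6 at every visit and 36 per arm. The sample size calculation itself is correct for a single test.

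**What to change.** Before any comparison between arms:

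1. Declare the executive function composite the primary variable.
2. Name one deciding mixed-model contrast, such as the arm difference at one named visit. One year is the only blinded assessment; post treatment comes first in the hypothesis. Either can be defended, and the choice should be stated with its reason.
3. Test the other visits in a fixed sequence after it, or label them supportive.
4. Make the individual tests secondary, either with confidence intervals and no efficacy claim or with Holm adjustment.
5. State that d = 0.6 and power 0.80 refer to that single contrast. The 45 per group then stands, with power 0.81 to 0.82 at 36 evaluable per arm. If 1 year is chosen, say why 0.6 is expected there, since nothing in the article ties it to that visit.

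The cost is a dated amendment and no additional participants. Recruitment is complete, and the trial therapist collects the end-of-treatment and 3-month data, so the record should show that the choice was made without sight of results by arm. The downside is that a significant single test, or a visit outside the sequence, can no longer be claimed as primary success.
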